### 11.6. Data Analysis

#### 11.6.1. Analysed Population

All participants enrolled into the study will be assigned to the following analysis sets:

- The intention to treat (ITT) analysis set. This will comprise all patients assigned to treatment.
- The Per Protocol analysis set. This set will comprise all participants who complete the study according to the protocol and who were compliant with assessment procedures (i.e., completed follow-up visits in accordance with local practice). It includes only those participants whose WLE specimens, and cavity shavings (if any) specimens were imaged within the time-window of approximately 145 minutes post-injection.

Further sensitivity analysis and summaries will be conducted based on sub-sets of the per protocol analysis set: e.g., subsets based on breast cancer diagnosis prior to surgery (invasive/DCIS), age etc.

A summary of the rate of decision to re-operate in the “Delayed LightPath® image set” (any participant for whom LightPath® Image of WLE and any cavity shaving specimens is outside the optimal time-window) will be presented as these participants will be excluded from the per protocol analysis set.

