### 11.6.2. Sample Size Determination

The primary endpoint of the study is to report the sensitivity and specificity of CLI + FAR LightPath® imaging for tumour detection compared to positive tumour detection using standard-of-care histopathology methodology (positive margin of a WLE sample).

Using an estimate of the incidence of positive excision margins on histopathology as 20%, with 95%-confidence ( $\alpha = 0.05$  two-sided) and with 10% precision, a sample size of 54 patients will provide sufficient power to detect sensitivity of 95% and specificity of 90% (Cameron and Baldock 1998). To allow for any potential drop-out or non-analysable subjects a total sample size of 60 patients will be enrolled to attain  $N = 54$  patients in the analysis.

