### 11.7.1. Analysis of the Primary Outcome Measure

The primary outcome will be the diagnostic performance of intraoperative CLI + FAR LightPath® imaging, assessed using a confusion matrix to describe the relationship between the results of tumour margin assessment (positive or negative) with CLI + FAR LightPath® imaging and standard-of-care histopathology (positive or negative) (gold standard).

| Standard-of-care histopathology |          |       |
|---------------------------------|----------|-------|
| Positive                        | Negative | Total |

|                                    |          |        |        |     |
|------------------------------------|----------|--------|--------|-----|
| CLI + FAR
LightPath®
imaging | Positive | a (TP) | b (FN) | a+b |
|                                    | Negative | c (FP) | d (TN) | c+d |
|                                    | Total    | a+c    | b+d    | n   |

Sensitivity =  $a/(a+c)$

Specificity =  $d/(b+d)$

Overall agreement =  $(a+d)/(a+b+c+d)$

TP = true positive; FP = false positive; FN = false negative; TN = true negative

The primary outcome measures are sensitivity, specificity and overall accuracy.

The following diagnostic accuracy statistics will be presented (as a percentage together with 95% exact confidence intervals):

- Sensitivity - The proportion of subjects with positive margin confirmed by histopathology who have a positive result on LightPath® Imaging.
- Specificity - The proportion of subjects with clear margin confirmed by histopathology who have negative result on LightPath® Imaging.
- Overall accuracy - The proportion of subjects whose margin status is correctly classified by LightPath® Imaging
- Positive predictive value - The probability of positive margin in subjects with a positive result on LightPath® Imaging.
- Negative predictive value - The probability of clear margin in subjects with a negative result on LightPath® Imaging.
- Positive likelihood ratio (LR+) = sensitivity/1-specificity
- Negative likelihood ratio (LR-) = 1-sensitivity/specificity
- Diagnostic odds ratio (DOR) = (TP/FP)/(FN/TN)

As a sensitivity analysis, the primary analysis will be repeated using the ITT analysis set and for the combined per protocol set.

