### 11.8. Termination / Drop-out

Recruitment will continue until up to 60 participants have been imaged. It is anticipated that approximately 10% of participants may drop out of the study or not be evaluable for the primary endpoint. The sample size of  $n = 54$  for the primary endpoint was selected including allowance of the assumption of 10% drop out. No other provision has been made for participant drop out. Patients who drop out will not be replaced.

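### The ITT sensitivity analysis repeats a 2x2 table with no place for a woman who has WLE histology but no usable LightPath result, and the formulas and verbal definitions treat her differently

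*Protocol*

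**What the plan says.** Section 11.7.1 sets LightPath (positive or negative) against histopathology (positive or negative) in a four-cell table. It prints sensitivity as a/(a+c), specificity as d/(b+d) and overall agreement as (a+d)/(a+b+c+d). The same section also defines these measures in words. Sensitivity is "The proportion of subjects with positive margin confirmed by histopathology who have a positive result on LightPath® Imaging", and specificity and accuracy are worded in the same way, over subjects classified by histology or over all subjects.

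Section 11.7 runs the primary analysis on the per protocol set. Section 11.6.1 limits that set to participants who complied with assessments and follow-up and whose specimens were imaged within the window of about 145 minutes. Section 11.7.1 then adds: "As a sensitivity analysis, the primary analysis will be repeated using the ITT analysis set and for the combined per protocol set".

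Of the ITT set, section 11.6.1 says "This will comprise all patients assigned to treatment"; the synopsis instead takes everyone who passes screening. Only one per protocol set is defined, so the combined one has no stated content.

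On expected losses, section 11.8 says: "It is anticipated that approximately 10% of participants may drop out of the study or not be evaluable for the primary endpoint". Section 11.6.2 says "a total sample size of 60 patients will be enrolled to attain" 54 in the analysis.

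**The concern.** The natural purpose of an ITT repeat is to show whether restricting the primary analysis to compliant, in-window participants flatters the test. One group matters most for an intraoperative test: women who had surgery and histology but for whom the device gave no usable answer. Such a woman is in the ITT set under either definition, but the table has no row for her.

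If the repeat is computed from the four cells, it is a complete-case analysis for that group. It would tend to agree with the primary result and could be read as evidence of robustness however many images failed. The outputs listed in section 11.7.1 do not include a count of non-evaluable results. The margin-level analysis there is planned on 60 x 6 = 360 margins, with no allowance for loss.

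The section also disagrees with itself about these women, so two analysts following the text could report different ITT estimates from the same data.

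**Working it through.** **Inputs.** Section 11.6.2 gives 60 enrolled, 54 analysed, 20% histology-positive, sensitivity 95%, specificity 90% and 10% precision. Section 11.8 gives about 10% for drop-out and non-evaluability together.

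**The plan's own figure.** 54/0.90 = 60, and 60 x 0.10 = 6 expected losses. This reproduces.

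**Formula against words.** Cells are read by position, with histology in the columns. Take a histology-positive woman with no LightPath result.
- By a/(a+c), she is in neither a nor c, so she leaves the denominator.
- By the verbal definition, she has a positive margin on histology, so she is in the denominator. She has no positive LightPath result, so she is not in the numerator and counts as a miss.

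The same split arises for specificity and accuracy. The two versions agree only if every woman classified by histology has a LightPath result.

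**Who the ITT repeat restores.** Let k be the number of the 6 who do have a LightPath result and histology, such as a late image or a missed follow-up visit. The ITT table then holds 54 + k and omits 6 - k. It ranges from 54 (k = 0) to 60 (k = 6). The protocol does not give k.

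**Size if all 6 have histology and no result, in proportion to margin status (assumption).** Positives: 60 x 0.20 = 12, of whom 1.2 are not evaluable. Negatives: 48, of whom 4.8 are not evaluable.

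| | Four-cell repeat | Not evaluable = incorrect | Not evaluable = correct |
|---|---|---|---|
| Sensitivity | 95% | 0.95 x 10.8/12 = 85.5% | (10.26 + 1.2)/12 = 95.5% |
| Specificity | 90% | 0.90 x 43.2/48 = 81.0% | (38.88 + 4.8)/48 = 91.0% |

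The falls are 9.5 and 9.0 points, close to the 10% precision in section 11.6.2. With m such women the lower values are 0.95 x (1 - m/60) and 0.90 x (1 - m/60). For m = 3 they are 90.25% and 85.5%; for m = 0 nothing changes.

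**Whole-patient illustration (assumed counts, exact 95% intervals).** Take 54 evaluable women, with 10 of 11 positives and 39 of 43 negatives correct: sensitivity 90.9% (58.7 to 99.8), specificity 90.7% (77.9 to 97.4). Add 6 unscored women and count them as incorrect:
- 1 positive, 5 negative: 10/12 = 83.3% (51.6 to 97.9) and 39/48 = 81.2% (67.4 to 91.1).
- 0 positive, 6 negative: 10/11 = 90.9% and 39/49 = 79.6%.
- 2 positive, 4 negative: 10/13 = 76.9% and 39/47 = 83.0%.

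With so few positives, one unscored woman moves sensitivity by several points.

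**The case against.** **The ITT repeat does useful work.** The one excluded group that section 11.6.1 names is the delayed-image set. Those women have images and fit the 2x2 table, as do women who were imaged but missed follow-up. This stands. A reader might infer that the repeat loses everyone it was meant to restore; that would be true only at k = 0.

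**The 10% is not a failure rate.** It covers those who "approximately 10% of participants may drop out of the study or not be evaluable for the primary endpoint". Because the primary endpoint uses the per protocol set, late images may be part of it. Women who leave before surgery have no histology and cannot be scored under any rule. Section 11.8 also says "Recruitment will continue until up to 60 participants have been imaged", so women never imaged may fall outside the 60. All of this stands, and the number affected could be zero.

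**The words already supply a rule.** Read literally, the verbal definitions score a missing result as incorrect. So the text does not establish that these women will be dropped. But the printed formulas point the other way, which leaves a conflict and not an answer.

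**This belongs in the SAP.** Handling of missing or indeterminate results is often placed there, and no SAP is at hand. That would answer mere silence. Here the protocol itself fixes the table, the formulas and the ITT repeat, and they disagree with its definitions.

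**Failures are recorded elsewhere.** Device deficiencies and reasons for delayed imaging go on the CRF (sections 10.8 and 8.6.4). That is true, but neither enters the accuracy estimates.

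**Conclusion.** The point holds in a limited form. Computed by its printed formulas, the ITT sensitivity analysis cannot show the effect of excluding women who have histology but no usable LightPath result, and section 11.7.1 gives two incompatible treatments of them. For late images and missed follow-up the repeat does what it should.

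The number affected is between 0 and about 6 of 60. The falls from 95% to 85.5% and from 90% to 81% are the limit under three assumptions: all 6 expected losses are test failures with histology, they are spread 20/80 by margin status, and each is scored as incorrect. A different split moves the two figures in opposite directions.

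A reader might go further and assume 9 failures, or half of 6 failures among the 12 positives (0.95 x 9/12 = 71%). The protocol supports neither: 9 exceeds its total expected loss, and nothing in it suggests that failures concentrate in women with positive margins.

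The primary per protocol estimate is not invalidated. The weakness lies in the check on it, which should be corrected before analysis.

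**What to change.** Replace the sensitivity-analysis sentence in section 11.7.1 with wording such as:

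*For all participants injected with FDG who have WLE histology, a 3x2 table (LightPath positive, negative or not evaluable, by histology) will be reported, with the number not evaluable. Sensitivity, specificity and accuracy will be recalculated with not-evaluable results counted as incorrect (lower bound) and as correct (upper bound). Participants without histology will be listed and not scored.*

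In addition:
- Make the verbal definitions and the formulas agree on whether a woman without a LightPath result is in the denominator.
- Have the sponsor define the combined per protocol set or delete it. Its intent cannot be recovered from the text.

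The cost is one extra table from data already collected, provided the CRF can record a LightPath reading as not evaluable. The lower bound will be less favourable than the complete-case figure whenever there are test failures. No clinical procedure changes.

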Analysis will be performed on the approximately 360 margins (60 patients x6 margins). The number of false positive, false negative, true positive, and true negative margins identified by intraoperative CLI + FAR LightPath® imaging will be reported.

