### 11.7.2. Analysis of Secondary Outcome Measures

- Agreement between margin status of cavity shavings as determined by intraoperative CLI + FAR LightPath® imaging and post-operative histopathology will be assessed similarly to the primary outcome measure (section 11.7.1).
- Agreement between margin status of WLE specimens as determined by intraoperative CLI + FAR LightPath® imaging and routine intraoperative specimen x-ray will be assessed similarly to the primary outcome measure (section 11.7.1).

- Re-operation rate within the study cohort will be compared to the general breast cancer population undergoing a WLE at Guy's Hospital. The re-operation rate within Guy's Hospital is routinely recorded, audited and have remained consistent at 20 – 25% over many years.  
By recording the time required to intraoperatively image and assess each specimen, the average time added to the operating procedure can be determined.

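### Section 11.7.1 gives two conflicting units for the primary analysis, subjects and about 360 margins; exact intervals suit the first and would be too narrow on the second

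*Protocol*

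**What the plan says.** Section 11.7.1 words its accuracy statistics per subject. Sensitivity is "The proportion of subjects with positive margin confirmed by histopathology who have a positive result on LightPath® Imaging", specificity is "The proportion of subjects with clear margin confirmed by histopathology who have negative result on LightPath® Imaging", and overall accuracy is "The proportion of subjects whose margin status is correctly classified by LightPath® Imaging". The predictive values are likewise probabilities in subjects. These statistics are to be given "as a percentage together with 95% exact confidence intervals", and no other interval method is named. Section 6.1 sets the primary outcome at the level of the WLE specimen, and section 11.6.2 sizes the study in patients (54 analysed, 20% with positive margins).

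The last paragraph of 11.7.1 changes the unit: "Analysis will be performed on the approximately 360 margins (60 patients x6 margins". It adds: "The number of false positive, false negative, true positive, and true negative margins identified by intraoperative CLI + FAR LightPath® imaging will be reported". It does not rank this against the per-subject analysis, and no rule is given for turning six margin results into one patient result.

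Section 11.7.2 carries the approach over to cavity shavings, where agreement with imaging "and post-operative histopathology will be assessed similarly to the primary outcome measure (section 11.7.1". One patient may contribute several shavings.

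**The concern.** A reader of 11.7.1 cannot tell whether the confusion matrix holds patients or margins. Section 11.7 says that the device's diagnostic performance will be judged on the primary endpoint analysis, so the main result depends on a unit that is stated in two ways. The choice changes the estimates, the prevalence behind the predictive values and the apparent precision, and it could be made after the data are seen.

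The interval method adds a second, conditional problem. Exact binomial intervals assume independent units. The six margins of one specimen share a tumour, an injection, an imaging session and a reader (under 8.6.4 the operating surgeon interprets the images). If the only named interval method were carried over to the margins, it would claim more information than the data hold.

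**Working it through.** **Inputs.** Six radial margins per specimen (8.6.8). 60 patients enrolled and 54 analysed, 20% positive, sensitivity 95%, specificity 90% (11.6.2). The protocol gives no intra-patient correlation (ICC), so a range is assumed.

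**1. The plan's own figure.** 60 x 6 = 360 margins, which reproduces. With 54 patients it would be 54 x 6 = 324.

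**2. The units are not interchangeable.**
- Specificity: 90% per margin, with independent margins, gives 0.9^6 = 0.531 per patient. Conversely, 90% per patient needs 0.9^(1/6) = 0.9826 per margin, a false-positive rate of 1.74% per margin.
- Prevalence: 60 x 0.20 = 12 positive and 48 negative patients. If each positive patient has one positive margin (assumption), there are 12 positive and 348 negative margins, and 12/360 = 3.3%.
- Positive predictive value at sensitivity 95% and specificity 90%: 0.19/(0.19 + 0.08) = 70% at 20% prevalence, against 0.0317/(0.0317 + 0.0967) = 25% at 3.3%.
- Wald half-width for a specificity of 90%: 1.96 x sqrt(0.09/48) = 8.5 points per patient, against 1.96 x sqrt(0.09/348) = 3.2 points per margin if all margins are taken as independent.

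**3. Exact intervals, if used on margins.** Design effect = 1 + (6 - 1) x ICC. The coverage column comes from a beta-binomial simulation of 54 patients x 6 margins, true per-margin specificity 90%, Clopper-Pearson interval on all margins.

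| Assumed ICC | Design effect | Effective margins of 324 | True SE / naive SE | Coverage of nominal 95% interval |
|---|---|---|---|---|
| 0 | 1.0 | 324 | 1.00 | about 96% |
| 0.1 | 1.5 | 216 | 1.22 | about 90% |
| 0.2 | 2.0 | 162 | 1.41 | about 85% |
| 0.3 | 2.5 | 130 | 1.58 | about 81% |

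With 60 x 6 margins the last three coverages are 91.5%, 86.3% and 81.8%. Separate runs agree to within about one to two points.

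The average half-width of the exact interval is about 3.4 points. The half-width needed is 1.96 x sqrt(0.09/324 x design effect) = 4.0, 4.6 and 5.2 points at ICC 0.1, 0.2 and 0.3. At the per-margin specificity of 98.26% from step 2, coverage is similar (91%, 86%, 81%) but the widths are smaller: about 1.6 points, against 1.7 to 2.3 needed.

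**4. Exact intervals per subject.** There is one WLE specimen, and so one result, per patient. Independence holds between patients and the intervals are valid.

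**5. Matching of location.** Suppose a patient counts as a true positive whenever any margin lights up. With one truly positive margin, per-margin sensitivity s and independent false positives at rate f on the other five, per-subject sensitivity is 1 - (1 - s)(1 - f)^5. At f = 0.0174, (1 - f)^5 = 0.916, so s = 60%, 80% and 95% read as 63.4%, 81.7% and 95.4%. The excess is 3.4, 1.7 and 0.4 points.

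**The case against.** The strongest defence is that the patient can be identified as the primary unit. Sections 6.1 and 11.6.2 and the per-subject definitions in 11.7.1 agree, and only one paragraph departs from them. That paragraph promises counts of margins, not intervals, while the exact intervals are attached to statistics worded per subject. A method for clustered data is commonly left to an SAP, and none is shown here. The analysis is mostly descriptive and no success threshold is stated.

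Much of this stands. A reader might infer that the protocol commits to exact intervals on the 360 margins. It does not say so, and the loss of coverage in the working is conditional on that use. What the defence does not remove is the unqualified statement, inside the primary-analysis section, that the analysis is performed on margins. Nothing elsewhere in the protocol subordinates it to the per-subject analysis.

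Two further readings are tempting and are not supported:
- That the per-subject definition materially overstates sensitivity because imaging and histology may be positive on different faces. The protocol is silent on how margins are combined. At the planned patient specificity of 90% the excess is 0.4 to 3.4 points. Figures such as 60% reading as 76%, or 80% as 88%, need a false-positive rate of 10% per margin, which implies a patient specificity of 53% if margins are independent. The margin-level counts would also help to expose a signal on the wrong face.
- That 360 is a wrong count because 54 patients give 324. The text says the number is approximate and 60 are to be enrolled, so the difference is trivial.

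**Conclusion.** The conflict of units is real and stands on the face of section 11.7.1: per-subject definitions are followed by an analysis on margins that is not marked as supplementary. It matters because the two units give different specificities (90% against 53% under independence), different prevalences (20% against about 3.3% with one positive margin per positive patient) and different apparent precision.

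The point about intervals holds conditionally. Used per subject, the exact intervals are sound. Used on margins, they would be too narrow whenever the intra-patient correlation is above zero, with coverage of about 90%, 85% and 81% at ICC 0.1, 0.2 and 0.3. Those ICC values are assumptions. The loss concerns mainly specificity-type statistics: with one positive margin per positive patient, margin-level sensitivity has no clustering.

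**What to change.** In section 11.7.1:
- State that the patient (WLE specimen) is the primary unit, with 95% exact intervals, and state how the six margin results on imaging and on histology form one patient result.
- Label the analysis of about 360 margins as supplementary. Any interval given at that level should allow for clustering by patient: a patient-level bootstrap, GEE, or a ratio estimator with robust variance.
- Optionally, add a sensitivity analysis in which a true positive requires imaging and histology to be positive on the same named margin. The six margins recorded under 8.6.8 make this possible.

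In section 11.7.2, apply the same allowance for clustering where a patient has more than one shaving.

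The cost is a few sentences and a few lines of code, with no new data. Margin-level intervals become wider; the per-subject exact intervals are unaffected.

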### 11.7.2. Analysis of Secondary Outcome Measures

- Agreement between margin status of cavity shavings as determined by intraoperative CLI + FAR LightPath® imaging and post-operative histopathology will be assessed similarly to the primary outcome measure (section 11.7.1).
- Agreement between margin status of WLE specimens as determined by intraoperative CLI + FAR LightPath® imaging and routine intraoperative specimen x-ray will be assessed similarly to the primary outcome measure (section 11.7.1).

- Re-operation rate within the study cohort will be compared to the general breast cancer population undergoing a WLE at Guy's Hospital. The re-operation rate within Guy's Hospital is routinely recorded, audited and have remained consistent at 20 – 25% over many years.  
By recording the time required to intraoperatively image and assess each specimen, the average time added to the operating procedure can be determined.

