| Intervention                              | Intraoperative CLI + FAR LightPath® imaging                                                                                                                                                                                                                                                                                                                                                                            |
| Comparator                                | Standard-of-care histopathology (gold standard)                                                                                                                                                                                                                                                                                                                                                                        |
| Product Regulatory Status and Study Phase | 
Imaging System:
The LightPath® Imaging System is an in vitro diagnostic device which has CE mark in Europe, in line with In Vitro Diagnostic Medical Devices 98/79/EC (post-marketing study).
 
Radiopharmaceutical:
F-FDG is a routinely used Positron Emission Tomography (PET) / Computed Tomography (CT) radiopharmaceutical
 
Study phase:
Phase II Study
 |
| Study Sponsors                            | King's College London
Guy's and St. Thomas' NHS Foundation Trust                                                                                                                                                                                                                                                                                                                                                    |
| Study Site                                | Guy's Hospital
[name]
United Kingdom                                                                                                                                                                                                                                                                                                                                        |

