Tumours fail to be completely excised because the surgeon only has the visual appearance of the tumour, palpation and specimen x-ray to differentiate malignant from benign tissue. A standardised approach to margin assessment can reduce residual disease and likelihood of re-excision (Bolger et al 2015, Merrill et al 2016). Currently available technologies for image-guided cancer surgery either have low sensitivity (for example, ultrasound, optical coherence tomography) or require lengthy regulatory development of novel contrast agents (e.g., targeted fluorescence or photoacoustic imaging). A number of techniques have been investigated including frozen section analysis and touch imprint cytology. However, no single technique has been accepted as standard of care due to issues of practicality, increased surgery time, limited clinical utility, limited sensitivity and specificity and cost (National Institute for Health and Care Excellence (NICE). (2009)). Consequently, less than 5% of hospitals that perform WLE currently utilise intra-operative cytology or frozen section pathology analysis of tumour margins (Bydlon et al 2012).

Optical imaging has been considered for intra-operative imaging since the original use of fluorescein in 1947 (Moore 1947). It offers an attractive solution to the problem of intra-operative tumour margin assessment, as it is fast and non-destructive. A variety of different methods of optical imaging have been proposed, including intra-operative radiography, radiofrequency spectroscopy, Raman spectroscopy, fluorescence spectroscopy and optical coherence tomography. Each has limitations, either in sensitivity and specificity, shallow penetration, poor definition or time and cost to develop targeted fluorescent agents.

In conclusion, a key problem that currently affects the success of WLE is the lack of accurate, real-time techniques to assess tumour margins intra-operatively. Therefore, there is a clear unmet need for new intra-operative techniques that can accurately and adequately assess tumour margins, thereby reducing the number of patients that need to undergo a re-operation.

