### 6.2. Secondary outcome measures

- Agreement between margin status of cavity shavings as determined by intraoperative CLI + FAR LightPath® imaging and post-operative histopathology.
- Agreement between margin status of WLE specimens as determined by intraoperative CLI + FAR LightPath® imaging and routine intraoperative specimen x-ray.
- Re-operation rate within the study cohort compared to general breast cancer population undergoing a WLE at Guy's Hospital.
- Time added to operating procedure.

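### Section 11.7.2 sends the LightPath versus specimen x-ray comparison to the histology-based accuracy analysis, which in effect puts x-ray in the gold-standard column of a secondary table

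*Protocol*

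**What the plan says.** Protocol section 6.2 lists as a secondary outcome "Agreement between margin status of WLE specimens as determined by intraoperative CLI + FAR LightPath® imaging and routine intraoperative specimen x-ray". Histology does not enter that outcome. Section 11.7.2 gives the method in one sentence: "routine intraoperative specimen x-ray will be assessed similarly to the primary outcome measure (section 11.7.1"). It states no adaptation.

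Section 11.7.1 cross-classifies LightPath against "standard-of-care histopathology (positive or negative) (gold standard"). From that table it derives sensitivity, specificity, overall accuracy, predictive values, likelihood ratios and a diagnostic odds ratio. Two of the definitions show the structure: "Specificity - The proportion of subjects with clear margin confirmed by histopathology who have negative result on LightPath® Imaging", and "Overall accuracy - The proportion of subjects whose margin status is correctly classified by LightPath® Imaging". The section also lists one symmetric quantity, overall agreement, (a+d)/(a+b+c+d).

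The synopsis names the comparator of the study as "Standard-of-care histopathology (gold standard"). No other gold standard is named. On current practice, section 3.1 says: "Tumours fail to be completely excised because the surgeon only has the visual appearance of the tumour, palpation and specimen x-ray" to tell malignant from benign tissue.

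**The concern.** Apart from overall agreement, and overall accuracy, which is the same quantity under another name, the statistics in section 11.7.1 depend on which variable sits in the reference column. For cavity shavings, which section 11.7.2 refers to 11.7.1 in the same words, histology stays in that column and the method fits. For the x-ray comparison the only other variable is x-ray, so it takes the column by default.

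The resulting figures would carry the names of accuracy measures without measuring accuracy. A margin that LightPath correctly flags and x-ray misses would lower LightPath's reported specificity and positive predictive value. Yet the study's rationale is that existing intraoperative tools, x-ray among them, leave positive margins behind. A reader of the report could take the table as evidence about LightPath's accuracy, or as a fair contest between the two tests. It is neither.

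**Working it through.** The plan gives no figure for this comparison, so there is nothing to reproduce. The check is structural, followed by an illustration of size.

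**Structure.** With x-ray in the columns, a patient who is LightPath-positive and x-ray-negative falls in cell b, whatever histology says. Specificity is d/(b+d), so every such patient lowers it. (The table in 11.7.1 prints the FN and FP labels of cells b and c the opposite way round from its own formulas. That is a separate matter; I follow the formulas.)

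**Inputs.**
- Prevalence: section 11.6.2 takes the "incidence of positive excision margins on histopathology as 20" per cent.
- LightPath against histology: sensitivity 0.95, specificity 0.90; analysed N = 54 (section 11.6.2).
- X-ray sensitivity Sx and specificity Cx: not in the document, so **assumed**, Sx 0.50–0.80 and Cx 0.70–0.90.
- Errors of the two tests independent given histology: **assumed**.

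**Formulas.**
- Apparent sensitivity = [0.2·Sx·0.95 + 0.8·(1−Cx)·0.10] / [0.2·Sx + 0.8·(1−Cx)]
- Apparent specificity = [0.2·(1−Sx)·0.05 + 0.8·Cx·0.90] / [0.2·(1−Sx) + 0.8·Cx]

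**Results.**

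| Assumed x-ray Sx / Cx | Apparent sensitivity | Apparent specificity |
|---|---|---|
| 50% / 70% | 0.119/0.340 = 35.0% | 0.509/0.660 = 77.1% |
| 50% / 90% | 0.103/0.180 = 57.2% | 0.653/0.820 = 79.6% |
| 60% / 85% | 0.126/0.240 = 52.5% | 0.616/0.760 = 81.1% |
| 80% / 70% | 0.176/0.400 = 44.0% | 0.506/0.600 = 84.3% |
| 80% / 90% | 0.160/0.240 = 66.7% | 0.650/0.760 = 85.5% |

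**What the apparent false positives contain, at 60%/85%.** Cell b has probability 0.2·0.40·0.95 + 0.8·0.85·0.10 = 0.076 + 0.068 = 0.144. In 54 patients that is 7.8, of whom 54·0.076 = 4.1 are histology-positive. About half of the apparent false positives would be correct calls.

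**A perfect LightPath.** At 100%/100% against an x-ray with 50%/90%, apparent sensitivity is 0.10/0.18 = 55.6% and apparent specificity 0.72/0.82 = 87.8%.

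**How far this depends on the assumed values.** Over a wider grid (Sx 30–90%, Cx 80–100%) apparent specificity is 75–88%, always below the true 90%. Apparent sensitivity behaves differently: it falls because of x-ray false alarms and stays at 95% if x-ray specificity is 100%.

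**With histology as reference for both tests.** LightPath keeps 95% and 90% whatever x-ray does. The expected counts are 54·0.20 = 10.8 histology-positive and 43.2 histology-negative patients. At 60% x-ray sensitivity, expected discordant pairs among the positives are 10.8·(0.95·0.40 + 0.05·0.60) = 4.4. A two-sided exact McNemar test gives 2·0.5⁵ = 0.0625 when all of five pairs favour one test and 2·0.5⁶ = 0.031 for six. At least six would be needed for p < 0.05.

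**The case against.** The outcome is labelled agreement, the cross-reference says that the method is similar rather than identical, and 11.7.1 includes a symmetric agreement line. Its sensitivity and specificity definitions mention histopathology explicitly, so they do not transfer word for word to x-ray. The choice among agreement statistics could be settled in a statistical analysis plan. These points stand in part: a reader might infer that the protocol declares x-ray a reference standard, and it does not. But the label settles little, because the primary outcome in section 6.1 is also called agreement and is still analysed with accuracy measures. Even overall agreement alone would count LightPath's correct detections missed by x-ray as disagreement, without showing which test was right.

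A reader might also infer that the study's conclusion about LightPath would be distorted. Section 11.7 rules that out: diagnostic performance is judged on the primary endpoint analysis, most analyses are descriptive, and secondary p-values only aid interpretation. No success criterion rests on the x-ray table.

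Nor is the absence of a paired comparison against histology an error in itself. The objective in section 6 concerns LightPath against histology, and superiority over x-ray is not a stated question. Adding the comparison is an improvement that uses data already scheduled.

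Finally, section 3.1 presents x-ray as one of few available tools and gives no accuracy for it. If the two tests tend to hit or miss the same margins, agreement would be higher than under independence and the illustrated ranges too low.

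**Conclusion.** The point holds as a flaw in how one secondary analysis is specified. Followed literally, the cross-reference yields accuracy statistics with x-ray as the truth, and histology-confirmed LightPath positives missed by x-ray are scored against LightPath. That conflicts with the protocol's naming of histopathology as its only gold standard. The consequence is a misleading secondary descriptive table; the primary analysis is untouched.

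The 35–67% and 77–86% ranges show possible size and are not a forecast. They rest on assumed x-ray accuracy, on conditional independence, and on the protocol's design values for prevalence and LightPath. The structural flaw depends on none of these.

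**What to change.** Replace the cross-reference for this outcome in section 11.7.2 with two statements.

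1. Direct LightPath/x-ray concordance is reported only as overall, positive and negative percent agreement, with kappa. Use the symmetric forms 2a/(2a+b+c) and 2d/(2d+b+c). Percentages conditional on the x-ray result would reproduce the same numbers under new names. Omit sensitivity, specificity, predictive values, likelihood ratios and the odds ratio from this table.
2. LightPath and x-ray are each scored against histopathology of the WLE specimen in the same patients. Report the paired difference in sensitivity among histology-positive patients and in specificity among histology-negative patients, with 95% confidence intervals, as descriptive estimates.

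The cost is a change of wording and a little more analysis. The schedule of events in section 2.4 already has specimen x-ray, LightPath imaging and histopathology of the WLE specimen in the same participants, and the outcome already requires a margin call from each test. No new procedure is needed.

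The limitation is precision. With about 11 histology-positive patients, even one proportion is poorly determined (10 of 11 has an exact 95% interval of 59% to nearly 100%), and a McNemar test would have little power. Present the sensitivity difference as an estimate, without a test.
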